## Abstract

Despite regularly used treatment asthma in both children and adults is not fully controlled. This is more prominent in certain disease subtypes, such as obese asthma. The vast complexity of asthma phenotypes and often overlapping endotypes emphasizes the need for implementing the concept of precision medicine in disease management. In order to address these concerns, an innovative and personalized programme for reducing excessive and maintaining a healthy body weight will be developed by experts from pharmaceutical and food industry (Belupo Inc. and Podravka Inc., Croatia) as well as clinical experts (Srebrnjak Children`s Hospital, Croatia). The programme will involve meals replacement (standard and innovative formulas), dietary program and nutritional counseling, physical activity and other individually tailored measures according specific disease phenotypes and underlying pathophysiological mechanisms in each participant. The outcomes of this study should contribute to better control of the underlying condition, reduction of the frequency and severity of symptoms and, consequently, in the improvement of the participant’s overall quality of life.

## Introduction

Asthma is the most common chronic disease in children, and numerous epidemiological studies show a constant increase in the incidence of asthma, with an almost certain continuation of a similar trend in the future [1]. Due to the complex and heterogeneous nature of the disease, there is still no cure and treatment is primarily symptomatic, serving to alleviate current symptoms, control inflammatory processes underlying the disease and prevent acute exacerbations. Currently, treatment outcomes in asthma exhibit a high degree of variability and depend largely on the individual characteristics of the patients [2]. Despite numerous studies on certain subtypes of asthma, knowledge about the causative agent and etiological factors is still insufficient, and therefore it is impossible to make a decision on the treatment regime that would suit an individual the most and to achieve optimal asthma control [2]. One of the most common comorbidities in asthma is obesity. In the last few decades, there has been an increase in the number of obese people to the extent of a global epidemic. This has also been observed in children, and the increasing trend continues as it has tripled over the last thirty years. Research has shown that excess body weight is an independent factor in the development of asthma and that there is a cause-and-effect relationship between body mass index and asthma. More than 40% of asthmatics are obese, and excessive body weight is a risk factor that leads to more frequent and severe symptoms [3,4]. Epigenetic modifications are considered one of the key triggers of pathophysiological mechanisms in asthma. It is believed that epigenetic modifications act as mediators of one’s exposure to environmental factors such as unhealthy diet and lifestyle that lead to excessive weight and obesity. Other than being a secondary mechanism (consequence) caused by disease pathophysiology, epigenetic mechanisms (such as DNA methylation and small non-coding RNA expression) may act as predisposing factors for asthma, and more specifically, asthma-related phenotypes (and specific endotypes) such as “obese asthma” [5]. Obesity is also associated with increased inflammation of the adipose tissue that may lead to an increase in systemic inflammation, with a number of immune cells and inflammatory mediators involved in this immune dysregulation [6].Current nutritional guidelines for weight reduction and maintenance of normal weight are based upon changes in lifestyle- energy-deficient diet, and regular physical activity. In situations where it is impossible to achieve a reduction in body mass by applying these guidelines, products with a reduced energy value, from the food category for special nutritional needs, can be used [7]

The aim of this research is to design and develop a personalized concept (regime) for weight reduction and maintaining a healthy body weight in order to gain better insight into the heterogeneity of disease subtypes under the broad term of “asthma”. More specifically, this research aims to identify new molecular and pathophysiological mechanisms involved in the development of asthma and its specific phenotypes which could, in turn, enable more effective management of the disease. Additionally, this research will potentially contribute to earlier and more precise diagnostics, optimization of current and development of novel, personalized treatment options in patients with specific asthma phenotypes (“obese asthma”). We hypothesize that weight reduction will help achieve better disease control and better treatment outcomes in both children and adults with obese asthma.

### Study endpoints

The primary endpoint of this study is to determine the effectiveness of a weight reduction diet program based on an innovative and standard product line (meal replacements) through actual reduction of the body mass (BM)/ fat mass (FM) of the participants in relation to their pre-trial body mass (BM)/fat mass (FM).

The secondary study endpoints include:

reduction of waistline and reduction of waist/hip and waist/height ratio;improvement of the participants` lipid profile (increase in HDL/LDL ratio) compared to initial values;improvement of the quality of life of participants;improvement of asthma control, decrease in the number and severity of asthma exacerbations in participants with asthma;decrease in systemic inflammation, decrease in oxidant stress biomarkers.

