### Assessments, measurements, diagnostic procedures and data collection

Recruitment started on 17^th^ January 2023. Upon recruitment, after the participants themselves and their parents/caregivers have agreed to participate in the study and signed the informed consent form, participants will undergo a physical examination, anthropometric measurements (height and weight for calculation of BMI and BMI percentiles, hip and waist circumference measurement, body composition assessments by Tanita MC-780MA multi frequency segmental body composition monitor based on bioelectrical impedance analysis (BIA) and by 7-site skinfold measurement using Harpenden skinfold caliper) along with other routine diagnostic tests as part of their asthma management plan, such as allergy tests (skin prick test and total and allergen-specific immunoglobulin E in the serum), lung function and bronchial challenge tests (spiroergometry) etc. Additionally, whole blood samples will be taken for subsequent transcriptomic analysis and isolation of PBMCs (peripheral blood mononuclear cells), as well as stool samples for metagenomic analysis of the gut microbiome. Blood samples leftover after routine diagnostic tests (blood count, lipid profile, glucose level etc. (Table 1) will be stored at -20°C for subsequent genetic analysis or at -80°C for evaluation of systemic inflammation. Stool samples will be stored at -20°C for subsequent microbiome analysis. Other relevant clinical data and data such as personal and family history, and demographics will also be collected.

**Table 1 pone.0306400.t001:** Features used in this study.

Baseline demographics	Gender, age
**Subjective clinical data**	Personal and family medical history, atopy status, allergic rhinitis (AR), atopic dermatitis (AD), food allergy and other comorbidities
**Objective clinical data**	Skin prick and total and specific e.g. test results, hematologic and biochemical blood test results (blood count, lipidogram, glucose level, creatinine, urates, total bilirubin, ALT^1^, AST^1^, GGT^1^, ALP^1^, electrolytes), urine analytes (with ketone bodies), comorbidity (ENT^2^ examination, pH probing with impedance for the reflux episodes monitoring for diagnostics of GERD/LPR^3^, other) lung function testing, FENO^4^, bronchial challenge tests, spiroergometry, treatment used, nutritional status (vitamins, minerals)

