**Fig 1 pone.0306400.g001:**
[figure not shown]
Study design and key timepoints.

The appearance of any exclusion criteria during the follow up phase will be a signal for participant exclusion from the study. During the entire course of the study, it will not be allowed to use other weight loss methods such as weight-loss medications or bariatric surgery.

Upon recruitment, participants will be randomized into 3 groups, according to weight loss plan: innovative formulation (1); standard (2) and control group (3) in a ratio of 2:2:1, respectively. Stratified randomization according to age, sex and baseline BMI will be provided to secure balanced groups according to their characteristics at baseline. Randomization plan will be done by the independent statistician not involved in recruitment and participants assessment prior to any recruitment. Trial participants, principal researchers, outcome assessors and data analysts will be blinded after intervention group allocation. Unblinding is permissible in case of severe adverse events or study withdrawals.

**Innovative group (1):** participants will use the innovative line of products intended for body weight reduction, that represent a meal replacement for weight management (liquid formulations and powders for resuspension- shakes and soups)- test group;**Standard group (2):** participants will use the standard line of products intended for weight reduction that represent a meal replacement for weight management with already proven clinical effectiveness (positive control);**Control group (3):** participants will receive personalized programme for a reduced low-calorie diet (balanced nutrition).

The standard product line will contain common ingredients and is currently commercially available [10], while the innovative product line differs will implement raw materials that are considered better sources of potentially bioactive components. Clinical studies suggest that these ingredients could have more health benefits due to their anti-inflammatory and antioxidant properties, including an impact on clinical parameters of the metabolic syndrome that is increasingly present in obese individuals [11].

All participants will implement physical activity regimes, personalized according to age, gender, health status, BMI, body composition, current physical fitness etc.

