### Statistical analysis

Sample size was calculated as 88: 88: 44 (N = 220 with the test for repeated measures using effect size of D = 0.5 (which represents a medium size clinical effect), SD = 1, power = 0.8 and alpha = 0.05 (minimum group size of 34) using a 15% drop-out rate. Analysis of variance for repeated measurements will be used to determine the effectiveness of individual programs on primary outcomes (BM/FM). The same analysis will be used to analyze secondary performance parameters and safety parameter variables. A chi-square test or Fisher’s test will be used to compare the occurrence of safety-related parameters between groups. The threshold for missing values will be set at 5%. If the missing values for certain variables exceed this threshold, these will be handled by imputing variables according to previously measured or observed values, that is the last observation will be carried forward. The analysis will be done as intention-to-treat (ITT) and as per-protocol (PP). P < 0.05 will be considered statistically significant with appropriate correction for multiple comparisons. The statistical analysis will be performed using STATISTICA 12 program (StatSoft, Tulsa, OK, USA).

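### The primary endpoint measures product effectiveness against participants' own pre-trial weight and names no efficacy comparison with the randomised control, so it cannot separate the product from effects shared by all arms

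*Protocol article*

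**What the plan says.** - **Endpoint.** The Protocol article, Study endpoints, defines effectiveness of the weight-reduction programme built on the two product lines as the reduction in body mass (BM) or fat mass (FM) "of the participants in relation to their pre-trial body mass (BM)/fat mass (FM"). The control group is not mentioned.
- **Analysis.** Statistical analysis states: "Analysis of variance for repeated measurements will be used to determine the effectiveness of individual programs on primary outcomes (BM/FM"). No group-by-time term and no arm-versus-control contrast is named. The only comparison described there as being between groups is the chi-square or Fisher test for safety events.
- **Arms.** The Follow up section (text after Fig 1) randomises 2:2:1 to innovative, standard and control. In the control arm, "participants will receive personalized programme for a reduced low-calorie diet (balanced nutrition"). The same section adds: "All participants will implement physical activity regimes".
- **Sample size.** Statistical analysis uses an "effect size of D = 0.5 (which represents a medium size clinical effect"), SD = 1, power 0.8, alpha 0.05, a minimum group size of 34 and 15% drop-out, and gives 88:88:44.

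**The concern.** Change from baseline is a sound variable for a weight-loss trial. The difficulty is the comparator. When the stated test of effectiveness is the participant's own starting value, everything that lowers weight in that arm counts for the product: calorie restriction, exercise, counselling, and the effects of time and of being observed. The design supplies calorie restriction and exercise to the control arm too, so the control could meet the same criterion.

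At stake is the main claim. Applied as written, the endpoint could support calling the innovative line effective when it adds nothing to a low-calorie diet. There is a second, smaller looseness: BM and FM are joined by a slash in both sections, without saying which is primary or whether both must succeed.

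**Working it through.** **Inputs.** D = 0.5, SD = 1, power 0.8, alpha 0.05, minimum group size 34, drop-out 15% and 88:88:44 come from Statistical analysis. Assumptions: tests are two-sided, and SD = 1 is the SD of the change. The article states neither. Evaluable numbers after drop-out are 88 × 0.85 = 74.8, taken as 75, and 44 × 0.85 = 37.4, taken as 37.

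**1. The plan's own figure.** For a paired t-test on change within one arm, the non-centrality is d√n.
- n = 33: 0.5 × √33 = 2.87, power 79.5%.
- n = 34: 0.5 × √34 = 2.92, power 80.8%.

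So 34 is the smallest n that reaches 80% in a before-after test. A 1:1 comparison of two arms with SD of change 1 needs 64 per arm by the t-test; 34 per arm would give about 53%. At 2:1 it needs 48 control and 96 product participants.

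**2. Does 34 prove a before-after design?** No. Other routes reach it:
- A two-group, two-time interaction with f = 0.25 and correlation 0.5 gives 34, although as the total of both groups.
- A 1:1 baseline-adjusted comparison at 0.5 SD, with an assumed baseline-outcome correlation of 0.7, has residual SD √(1 − 0.7²) = 0.714 and needs 34 per group.
- A 1:1 change-score comparison with an assumed correlation of 0.73 has SD of change √(2 × 0.27) = 0.735 and needs 35 per group.

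The article gives no correlation and says only that a test for repeated measures was used.

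**3. What a before-after criterion would do.** Assume that every arm loses 0.5 SD and the true product effect is zero.
- Product arm, n = 75: non-centrality 0.5 × √75 = 4.33, critical value 1.99, probability of significance about 99%.
- Control arm, n = 37: non-centrality 0.5 × √37 = 3.04, critical value 2.03, probability about 84%.

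Both arms would usually be declared effective. The gap between 99% and 84% comes only from the 2:1 allocation.

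**4. Power of the randomised contrast.** For product versus control at D = 0.5, SD of change 1 and 75:37, the non-centrality is 0.5 / √(1/75 + 1/37) = 2.49 and the critical value 1.98. Power is about 69% at two-sided 0.05.

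This depends on what SD = 1 means. If it is a cross-sectional SD with baseline-outcome correlation r, the SD of change is √(2(1 − r)):

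| r (assumed) | SD of change | Power, 75:37 |
|---|---|---|
| 0.3 | 1.18 | 55% |
| 0.5 | 1.00 | 69% |
| 0.7 | 0.77 | 89% |

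**The case against.** The strongest reply is that the endpoint section only defines a variable and sets no within-arm decision rule. The trial is randomised and stratified, calls the standard arm a positive control, plans intention-to-treat and per-protocol analyses, and promises a correction for multiple comparisons. A three-arm repeated-measures ANOVA ordinarily contains a group-by-time term, and its exact contrasts may be set out in a fuller document that is not shown.

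Much of this stands, and it rules out some stronger readings:
- A reader might infer that the randomisation is discarded. The documents do not support that, because a comparison with control is possible under the named analysis.
- A reader might infer that 34 is a before-after number and so settles the question. It is consistent with one, but step 2 shows between-arm routes to the same figure.
- A reader might put power far lower by applying Bonferroni to two outcomes and three pairwise contrasts. The article does not state that correction.
- A reader might extend the point to asthma, since the Introduction says "We hypothesize that weight reduction will help achieve better disease control and better treatment outcomes". That is motivation for a secondary endpoint; no before-after asthma test is specified, so arguments about season or regression to the mean have no stated analysis to attack.
- A reader might object that body composition is measured by "bioelectrical impedance analysis (BIA) and by 7-site skinfold measurement". Which method supplies FM is detail that a fuller document commonly settles.

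The reply does not remove the core point. The article does not merely leave the comparator open. It states one, the participant's own baseline, and the analysis section speaks of "to determine the effectiveness of individual programs on primary outcomes (BM/FM") without naming another.

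**Conclusion.** The point holds as a wrongly stated primary criterion. Because all arms restrict calories and exercise, reduction from pre-trial BM or FM cannot by itself show that a product works. Under an assumed shared loss of 0.5 SD and no product effect, the before-after test would be significant about 99% of the time in a product arm and about 84% in the control arm. Those figures illustrate the criterion applied literally; they do not predict what the trial's analysts will do, since a group-by-time test may be intended.

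A comparison with control is neither the stated criterion nor shown to be the basis of the sample size. Its power at 75:37 is about 69% if the SD of change is 1, and 55% to 89% over the assumed correlations above. The unresolved choice between BM and FM is a real but secondary ambiguity.

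**What to change.** 1. Keep change from baseline as the variable, and state the primary endpoint as the between-arm difference in that change at one fixed visit, tested as the group-by-time contrast of product versus control.
2. Place innovative versus standard in a prespecified order with the control comparison, so that the multiplicity rule is explicit.
3. Name one of BM or FM as primary and the other as secondary.
4. Report within-arm change as descriptive only.
5. Restate power for product versus control, saying whether SD = 1 is the SD of change or cross-sectional and, if cross-sectional, which correlation is assumed.

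The cost is wording in the endpoint and analysis sections, fixed before unblinding; no new data are needed. The downside is that the claim becomes harder to win, and the restated power may fall below the stated 80%: about 69% at D = 0.5 with SD of change 1.

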## Materials and methods

Research and development activities within this study will take place at the Srebrnjak Children`s Hospital, Zagreb, Croatia (SCH) and Belupo Inc. and Podravka Inc., Koprivnica, Croatia over 33 months and encompass four different phases: (I) development of a formulation for food products intended for the loss of excess body weight, (II) development of a personalized program for excess body weight, (III) clinical study, and (IV) development of multidisciplinary nutritional support.

The first research phase employs the defining of the target product composition (food products for body weight reduction). In the following phase, based on the established functional-technological characteristics of the products, a long-term programme for excess body weight reduction will be developed. The program will be adaptable to the personalized needs of different target groups of participants.

In the third phase of research activities a clinical study will be conducted. In the final phase of this research a personalized multidisciplinary support programme (with a counseling center) for the reduction of excessive body weight will be created encompassing innovative food products for weight loss.

### Study population

Overweight and obese participants (adults and children) will be recruited in a prospective interventional case-control clinical study at the Outpatient clinical at Srebrnjak Children`s Hospital, Zagreb, Croatia. The sample size is set to 240 participants, adults (>18 years) and children aged 12-18 years, with 1/3 of the participants being children (approximately 160 adults and 80 children). Written informed consent will be obtained from all participants and their parents/caregivers. The study was approved by the local Ethics committee at SCH (on 14^th^ March 2022, Ref. no.: 04-301/1-22; Supplementary material). The study has been registered at ClinicalTrials.gov PRS (ID: NCT05980663, NCT05733871).

The study involves participants (adults and children aged 12 to 18 years, of both sexes) who have themselves signed a written informed consent (for pediatric participants both the children and their parents/caregivers will sign the informed consent, according to local legislation), i.e., those who agreed to participate in the study and do meet the criteria for inclusion. The participants will be assessed for inclusion and exclusion criteria on their first study visit after signing the informed consent. Criteria for inclusion and exclusion will be assessed by a specialist physician (pediatric allergy specialist) and an occupational medicine specialist.

The main inclusion criteria are overweightness and obesity (for adults- BMI > 27 kg/m^2^, for children- ≥ 90^th^ BMI percentile), to be able to correct for differences in body composition (e.g., higher BMI due to higher muscle mass in semi-professional or professional athletes). Additional inclusion criteria will include: physician diagnosed asthma (according to ERS/ATS guidelines) for at least one year, being on a stable dose of anti-inflammatory treatment for at least one month according to GINA (Global Initiative for Asthma) guidelines [8,9], clinically significant allergy to indoor and outdoor allergens, with positive skin prick test (SPT) and specific IgE levels (>0.7 kUA/L).

Exclusion criteria for adults are: acute respiratory infection; use of systemic corticosteroids, antidepressants, cytostatics, hormone (replacement) treatment, beta-blockers; recent asthma-related visit to emergency department (in the past three weeks); pregnancy and breastfeeding; coexistence of other serious chronic illnesses, such as uncontrolled diabetes mellitus requiring insulin therapy and other endocrine disorders, cardiovascular disorders and other chronic diseases (including malignancies), chronic inflammatory diseases of the gastrointestinal tract, mental disorders; currently on or recently gone through a weight loss programme (in the past 3 months); an unwanted or uncontrolled loss of body weight > 5% in the past 6 months; bariatric surgery in the past 6 months; use of medications that influence appetite; eating disorders; unstable thyroid disease.

Exclusion criteria for children are: known inborn or perinatal pulmonary disease; known congenital and other serious chronic illnesses (such as malignant diseases, chromosomal aberrations, neurological disorders that affect oral motor skills, chronic gastrointestinal disorders or severe metabolic disorders), pulmonary malformation; oxygen therapy after birth with a duration of more than 24 h; ventilator support or mechanical ventilation after birth; diagnosis of cystic fibrosis; primary ciliary dyskinesia; heart failure diagnosed after birth affecting pulmonary circulation; major respiratory diseases such as, e.g., interstitial lung disease. Moreover, participants were excluded from study visits and biomaterial collection in the case of fever of at least 38.5 °C during the last two weeks prior to the planned visit.

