**Anthropometric data**	Height, weight, BMI^5^, BMI percentile for children, hip and waist circumference and hip/waist ratio, body composition (% fat mass, % fat free mass)
**Systemic inflammation data**	hsCRP^6^, leptin, other serum markers
**Genetic data**	Epigenetic status (DNA^7^ methylation), genetic expression patterns, gut microbiome
**Dietary data**	Dietary intake, food diaries, dietary questionnaires

^1^Liver enzymes (Alanine Aminotransferase, Aspartate transaminase, Gamma-glutamyl transferase, Alkaline phosphatase).

^2^Ear, Nose, and Throat examination.

^3^Gastroesophageal reflux disease/laryngopharyngeal reflux.

^4^Fraction of Exhaled Nitric Oxide.

^5^Body Mass Index.

^6^C-reactive protein.

^7^deoxyribonucleic acid.

Their dietary patterns and food intake will be assessed by food frequency questionnaire (FFQ), 14-point Mediterranean Diet Adherence Screener- MEDAS (or children version – KIDMED), The Three-Factor Eating Questionnaire (TFEQ-R1) and 3-day food diary at the beginning and end of the study.

Participants will be assigned specific and adapted physical exercise programmes and vital and other parameters (heart rate, respiration, step count etc.) will be collected by smart bands.

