The study protocol is defined in detail in Supplementary material. This study will encompass 4 phases of different duration and design for adults and pediatric participants): initial phase (intensive), active phase, stable phase and monitoring phase, preceded by an entry phase of adaptation to the study protocol (duration of entry phase: 2 weeks). The study phase diagram is shown in Fig 2.

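### Absolute body mass/fat mass against baseline is the primary endpoint for adults and growing adolescents alike, so growth biases the pre-post reading and adds avoidable variance between arms

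*Protocol article*

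**What the plan says.** All of the following is in the protocol article.

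- **Study endpoints.** Effectiveness is to be shown "through actual reduction of the body mass (BM)/ fat mass (FM) of the participants", relative to each participant's own pre-trial value. The measure is absolute, with no standardisation for age or height.
- **Study population.** The planned total is 240, and the age split is given as "with 1/3 of the participants being children (approximately 160 adults and 80 children". Entry is on an adult BMI cut-off for adults but on a BMI percentile in the young ("for children- ≥ 90").
- **Table 1.** The anthropometric data include "BMI percentile for children" and body composition as percentages of fat and fat-free mass. Neither is named as the primary measure.
- **Statistical analysis.** There is one sample-size calculation (D = 0.5, SD = 1, power 0.8, alpha 0.05, minimum group 34, 15% drop-out) and one repeated-measures ANOVA on BM/FM. No age factor is mentioned.
- **Follow up.** Anthropometry is monthly for everyone. Randomisation is 2:2:1, stratified by age, sex and baseline BMI. The diet programme has "4 phases of different duration and design for adults and pediatric participants".
- **Introduction.** The hypothesis is about benefit "in both children and adults with obese asthma".

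**The concern.** Adolescents gain height and weight during follow-up whether or not a weight programme works. A child who improves clearly for age and height may show little or no fall in kilograms. The protocol uses a percentile to decide which children are overweight, then returns to the raw scale to decide whether they improved.

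Two things are at stake. First, a change from baseline in kilograms, averaged over adults and children, understates the improvement in children and so in the pooled sample. Second, when arms are compared, the difference in mean change between age groups goes into the error term unless age group is in the model.

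A further point concerns interpretation. The diet phases differ by age, so an arm-by-time effect pooled over ages averages different regimens at the same month, and does not describe either age group.

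**Working it through.** **1. The plan's own minimum group size.** A paired (one-sample) t-test on change with d = 0.5, two-sided alpha 0.05 and power 0.80 gives n = 33.4, rounded up to 34, which is the stated figure. Sidedness is not stated; a one-sided paired test would give 27. A two-sample comparison at 2:1 with d = 0.5 would need 48 controls. The figure of 34 therefore matches a within-group pre-post test.

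**2. Effect of growth on the pre-post contrast.** Assumed, not in the documents: true loss 3 kg, SD of change 6 kg (so d = 0.5), and growth gain g of 2 or 5 kg over follow-up in the one third who are children.

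- Apparent pooled loss = 3 − g/3
- Pooled SD = √(36 + (1/3)(2/3)g²)

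| g (kg) | apparent loss (kg) | pooled SD (kg) | apparent d | paired-test power at n = 34 |
|---|---|---|---|---|
| 0 | 3.00 | 6.00 | 0.50 | 81% |
| 2 | 2.33 | 6.07 | 0.38 | 58% |
| 5 | 1.33 | 6.45 | 0.21 | 22% |

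At g = 5, children with a true 3 kg benefit show a mean gain of 5 − 3 = 2 kg.

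**3. Effect on the between-arm difference.** The expected shift from growth is g/3 (0.7 to 1.7 kg for g of 2 to 5) in every arm, control included, because allocation is stratified by age. It drops out of the difference. A simulation with 4 kg growth in one third of participants and a true difference of −2.50 kg returned −2.53 kg. The small gap comes from rounding the child counts (29 of 88 versus 15 of 44).

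**4. Effect on between-arm power.** Inputs: N = 240 from the Study population section, 2:2:1, 15% loss. 240 × 0.85 = 204, and 204/5 = 40.8, so about 41 controls against 82 per product arm. Assumed: within-age-group SD 6 kg, true difference 3 kg, and a gap between age groups in mean change of 5 or 8 kg, whether from growth or from the different regimens. Two-sample t-test, two-sided 0.05, age group not in the model:

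| gap (kg) | pooled SD (kg) | d | power |
|---|---|---|---|
| 0 | 6.00 | 0.50 | 74% |
| 5 | √(36 + (2/9)25) = 6.45 | 0.47 | 68% |
| 8 | √(36 + (2/9)64) = 7.09 | 0.42 | 59% |

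**5. What adjustment recovers.** Putting age group in the model removes the (2/9)gap² term. If growth is the same for every child, power returns to 74%. If growth also varies between children with an assumed SD of 1.5 to 3 kg, the SD becomes √(36 + 1.5²/3) = 6.06 to √(36 + 3²/3) = 6.24, and adjusted power is 73% to 70%. Standardising the child outcome for age and sex is aimed at part of that remainder.

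**6. Children alone.** 80 at 2:2:1 is 32:32:16, or about 27:27:14 after 15% loss. Power for 27 versus 14 at d = 0.5 is 32%.

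**The case against.** The case on the other side is substantial, and several stronger readings that a reader might infer fall to it.

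- **That growth masks the treatment effect or works against the products.** It does not in the randomised comparison. Age-stratified allocation gives each arm the same expected growth. This objection stands in full; bias is confined to the pre-post reading.
- **That the repeated-measures time axis differs between age groups.** The Follow up section gives one monthly calendar for all, and nothing says that the ANOVA levels are phases. What differs by age is the diet phase in force at a given month, which affects interpretation, not timing.
- **That body mass alone is the primary outcome.** The endpoint is BM/FM. Fat mass is probably less affected by growth and is recorded as a percentage. But the endpoint as worded is still an absolute reduction, and body mass remains part of it. Waist/height ratio is a growth-relevant measure for all participants, but only a secondary one.
- **That growth is counted as treatment failure.** The protocol defines no responder or failure category.
- **That child arms below 34 contradict the plan.** The 34 is a minimum per trial arm, and no separately powered child test is promised. The 32% is a caution for reporting, not an inconsistency.
- **That age is certainly left out of the model.** The article states no covariates either way, and a fuller plan may add age. The power loss in step 4 is therefore conditional. The choice of endpoint is not: the article states it.

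It is also fair that the reference power is already 74% at 41 versus 82 (and about 70% if the 220 in the Statistical analysis section is used), so most of the shortfall from 80% at a 5 kg gap has other causes.

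**Conclusion.** The concern holds in a limited form. The endpoint is fixed as an absolute change from baseline and fits a third of the sample badly. Growth biases the pre-post contrast, on which both the endpoint wording and the minimum of 34 rest. Under the assumed values, the apparent pooled effect falls from 0.50 to 0.38-0.21 SD.

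The randomised comparison is not biased. Its cost is precision: 74% power falls to 68-59% under an assumed 5-8 kg age-group gap and SD of 6 kg, if age group is left out of the model, and most of this is recoverable. All growth, gap and SD figures are assumptions; the documents give none.

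This is worth changing because the remedy uses data already being collected. It is not a flaw that invalidates the trial.

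**What to change.** 1. State that effectiveness is judged on the between-arm difference in change, not on pre-post change within an arm.
2. For children, use change in age- and sex-standardised BMI (BMI z-score), with fat mass as percent fat mass. For adults, keep change in body mass/fat mass.
3. Put the age stratum, with its interactions with arm and time, in the repeated-measures model. Alternatively, estimate the standardised arm difference in each age group and combine the two with stratum weights.
4. Report each age group's estimate with a confidence interval, and say that the child-only results are not separately powered.

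**Cost.** No new visits, measurements or participants: height, weight, BMI percentile and body composition are already taken, and age is already a randomisation factor. The overall result would be on a standardised scale, so kilograms should still be reported for adults. Recruitment began on 17 January 2023, so this is a change to the primary outcome of a registered trial. It needs a dated amendment, made before outcome data are examined by arm.
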